### Statistical analysis

A prior retrospective comparison of quetiapine and pimavanserin estimated an effect size of 0.58 for psychosis outcomes^46^. Based on this estimate, a two-tailed α of 0.05, and 80% power, a total sample size of 94 participants (47 per arm) was calculated using a standard two-sample comparison of means. Because this power analysis was derived from retrospective data and therefore represents an imperfect estimate of the true effect size, an interim analysis has been planned for once 60 participants enrolled, including a repeat power calculation if the primary endpoint has not yet been reached.

Descriptive statistics were used to characterize the participants. Chi-squared tests were used to compare categorical variables between groups, except for comparison between trial participants with the overall clinic cohort, for which a chi-squared goodness-of-fit test was used.

Planned analyses for the trial outcomes include t-tests for continuous variables with normally distributed data, Wilcoxon rank-sum tests for non-normally distributed continuous data, and chi-squared tests for categorical variables, to compare characteristics between groups. Data will be analyzed on an intention to treat basis, with missing data omitted. Multivariable generalized linear models (or parametric lifetime model for medication discontinuation) with suitable outcome distributions will be used to compare treatment effects adjusting for covariates. Sensitivity analyses will be conducted to assess estimation biases.

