In this study, we describe a pragmatic randomized trial comparing two antipsychotic treatments, pimavanserin and quetiapine, for psychosis in LBDs over a period of six months. While pimavanserin is the only medication approved by the U.S. Food and Drug Administration specifically for PD psychosis, its real-world use is limited by cost, insurance restrictions, and concerns about its comparative effectiveness. Quetiapine is often prescribed as a more accessible and cost-effective alternative^24,25^. However, existing evidence for quetiapine use in LBDs is mixed, with studies limited by small sample sizes and inconsistent results, further illustrating limitations of explanatory RCTs^26–31^.

By integrating research into standard clinical workflows, this pragmatic trial aims to produce findings that are more applicable to real-world practice in a diverse population. To date, 60 participants (mean age 76 years) have enrolled (Table 1), comprising 43% of patients seen by the enrolling clinicians for this study (*n* = 141), and 25% of all patients (*n* = 239), with PD or DLB who were seen in the University of Texas Health Science Center at San Antonio (UTHSCSA) Neurology Clinic and prescribed quetiapine or pimavanserin during the study period, as identified using SlicerDicer (Epic Systems Corporation, Verona, WI). Thirty (50%) were randomized to receive pimavanserin and 30 (50%) to quetiapine. Of the total cohort, 52 (87%) are diagnosed with PD (including those with PD dementia (PDD)) and 8 (13%) with DLB. Twenty-four (40%) are women and 23 (38%) identify as Hispanic. At the time of this report, a total of 56 participants are enrolled and retained (93%), including 48 who have completed the study and 8 who remain active with a mean time since enrollment of 130 days. Four participants were lost to follow-up (2 due to death and 2 due to relocation or withdrawal). Among the 4 participants lost to follow-up, all are men and White, including 1 who identifies as Hispanic and 1 with unknown ethnicity. Based on ZIP codes, participants have a mean Social Vulnerability Metric (SVM) score of −0.41 (39.7 percentile), where negative SVM scores and lower SVM percentiles indicate less social vulnerability^32^.

**Table 1 Tab1:** Baseline Characteristics of Enrolled Participants

Patient Characteristics	Total = 60
Age, mean ± SD (years)	76 ± 8
Sex, male, *n* (%)	36 (60)
Race, White, *n* (%)	56 (93)
Hispanic Ethnicity, *n* (%)	23 (38)
Social determinants of health	

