### Randomization and interventions

Participants are randomized in a 1:1 ratio to receive either quetiapine or pimavanserin. Seven clinicians participated in enrollment. Randomization is stratified by clinic site, performed using the NIH Clinical Trials Randomization Tool (https://ctrandomization.cancer.gov/tool/), and implemented using sequentially numbered, opaque, sealed envelopes. The allocated intervention is unblinded to all immediately after assignment. Consistent with the pragmatic design, clinicians retain full discretion in treatment decisions. All study medications are prescribed, managed, and adjusted as part of routine care by the treating clinicians, who do not have access to the random allocation sequence.

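### The 94 participants are the number that must be analysed for 80% power; with no allowance for loss and missing data omitted, 94 enrolled gives about 76–77.5% at the loss seen so far

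*Protocol article*

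**What the plan says.** The sample-size statement is in the Statistical analysis section of the Methods. A prior retrospective comparison "estimated an effect size of 0.58 for psychosis outcomes". From that, with "a two-tailed α of 0.05, and 80% power", the article reports that "a total sample size of 94 participants (47 per arm) was calculated using a standard two-sample comparison of means". Allocation is equal: "Participants are randomized in a 1:1 ratio to receive either quetiapine or pimavanserin".

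The same section sets the rule for incomplete data: "Data will be analyzed on an intention to treat basis, with missing data omitted".

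The enrolment report in the opening main text, which runs on under the Abstract heading, gives the follow-up status of the first 60 participants: "a total of 56 participants are enrolled and retained (93%), including 48 who have completed the study and 8 who remain active". The rest are accounted for as follows: "Four participants were lost to follow-up (2 due to death and 2 due to relocation or withdrawal".

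An interim analysis is planned once 60 are enrolled, "including a repeat power calculation if the primary endpoint has not yet been reached". The reason given is that the retrospective effect size is an imperfect estimate. Loss to follow-up is not mentioned there.

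**The concern.** A calculation for two means returns the number of participants whose outcome enters the comparison. The article gives that number as the total sample size. Because participants without an outcome are dropped from the analysis, every loss reduces the analysed number below the one that supports 80%. The trial already has losses, two of them deaths.

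What is at stake is the accuracy of one planning figure. A reader will take 80% as the power of the 94-participant design. Any re-sizing at the interim that repeats the same method would carry the same gap into the new target.

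**Working it through.** **Inputs.** From Statistical analysis: d = 0.58, two-sided α = 0.05 (z = 1.960), power 80% (z = 0.842), 47 per arm, missing data omitted. From Randomization and interventions: 1:1 allocation. From the enrolment report: 60 enrolled, 48 completed, 8 active, 4 lost. The article states no planned dropout rate, so the observed loss is used as an assumption and split equally between arms.

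**1. Reproduce the article's figure.** Normal approximation, per arm:

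n = 2(1.960 + 0.842)² / 0.58² = 2 × 7.851 / 0.3364 = 46.7, so 47 per arm and 94 in total.

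This is an exact match with no inflation. The t-based requirement is 47.6, so 48 per arm (96 in total).

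Power at 47 per arm with nobody lost:
- Normal: Φ(0.58 × √(47/2) − 1.960) = Φ(0.852) = 80.3%.
- t-test (noncentral t): 79.5%.

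**2. Observed loss.** 4/60 = 6.7% of those enrolled. Among those whose follow-up has ended, 4/(48 + 4) = 4/52 = 7.7%.

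**3. Analysed number out of 94.**
- 6.7% loss: 47 × (1 − 0.0667) = 43.87 per arm, about 88 in total.
- 7.7% loss: 47 × (1 − 0.0769) = 43.38 per arm, about 87 in total.

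**4. Power at d = 0.58 with those numbers.**

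| Loss | Analysed per arm | Normal approximation | t-test |
|---|---|---|---|
| 0 | 47 | 80.3% | 79.5% |
| 6.7% (4/60) | 43.87 | 77.5% | 76.6% |
| 7.7% (4/52) | 43.38 | 77.1% | 76.1% |
| 10% (assumed) | 42.3 | 76.0% | 75.1% |

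Within one method, loss costs 80.3 − 77.5 = 2.8 to 80.3 − 77.1 = 3.2 points (normal), or 79.5 − 76.6 = 2.9 to 79.5 − 76.1 = 3.4 points (t-test).

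**5. Effect detectable with 80% power.** At 44 per arm: (1.960 + 0.842) × √(2/44) = 2.802 × 0.2132 = 0.597, or about 0.60.

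**6. Enrolment that would keep 80% at 6.7% loss.** 47/(1 − 0.0667) = 50.4, so 51 per arm and 102 in total. On the t-based count, 48/(1 − 0.0667) = 51.4, so 52 per arm and 104 in total.

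**7. How firm the loss rate is.** The exact 95% interval for 4/60 is 1.8% to 16.2%. At those limits the analysed number per arm is about 46.1 and 39.4, and power by the normal approximation is 79.5% and 73.0%.

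**The case against.** **The arithmetic is right, and this is a condensed article.** A reader might infer that 94 was miscalculated. It was not: it reproduces exactly. It is also true that an article commonly leaves a dropout allowance to the full protocol. But the 94 equals the uninflated answer, so no fuller document can place an allowance inside it. What stands is that the fault lies in presenting an analysed number as the total, not in the computation.

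**The drop is smaller than 80% against 76% suggests.** A reader might attribute all four points to loss. Part of that gap is the difference between the normal approximation and the t-test, which is convention. Within either method, loss costs about 3 points. This stands, and the range 76–77.5% is fairer than a single figure.

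**The rank test.** A reader might infer that power falls further because the plan uses the Wilcoxon test for non-normal data. The documents do not support a figure for this. The familiar efficiency of the rank test relative to the t-test is for normal data, where the plan uses the t-test. For non-normal data the rank test can do better or worse. The article also does not state the range of the item scores, and the endpoint is a change in them.

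**The target is provisional.** Recruitment is paused for the interim analysis, and a repeat power calculation may change the 94. That is a fair reason not to call the trial's final power deficient. But the recalculation is conditional and is motivated only by uncertainty in the effect size, so nothing in the article says that loss will be taken into account.

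**The lost may not all be missing.** The Data collection and follow-up section provides for phone contact with patients who do not return, and the outcome window extends by 3 months. The article does not say that all four lack the primary outcome. Phone contact cannot recover the outcome of a participant who died before it was collected, but the two who relocated or withdrew could in principle have data. The 4/52 rate also leaves out eight active participants who are a mean of 130 days into follow-up, so it probably runs high.

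**Effect size and adjustment matter as much or more.** With no loss, t-test power at 47 per arm is 67% at d = 0.50 and 82% at d = 0.60, a wider swing than loss produces. Covariate-adjusted models are also planned. The t-based requirement is 47.64 per arm, so covariates explaining about 1 − 43.87/47.64 = 8% to 1 − 43.38/47.64 = 9% of outcome variance would restore 80%. That share is an assumption, and the stated 80% was computed for an unadjusted comparison. These points limit the importance of the finding but do not make the stated figure correct.

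**Conclusion.** The point holds, as a small correction. The 94 is the number that must be analysed for 80% power at d = 0.58, while the plan omits missing data and already reports losses. At 94 enrolled and the observed loss, power for the unadjusted comparison is about 76–77.5%, and 80% power applies to d of about 0.60.

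This rests on four assumptions: the observed loss rate of 6.7–7.7% continues, although it comes from only four events; all those lost have no 6-month NPI-Q; losses are about equal between arms; and 0.58 is the true effect. The absence of an allowance in the 94 is certain. The exact size of the shortfall is not.

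The documents do not support saying that the sample-size arithmetic is wrong, that power falls materially below this range, or that the trial will finish underpowered whatever the interim analysis decides.

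**What to change.** Use one of two wordings in the Statistical analysis section:

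- Restate the power: 94 enrolled, about 87–88 analysable at the observed loss of about 7%, gives about 76–77% power for d = 0.58 (80% for d of about 0.60) with the unadjusted test.
- Or define 94 as the number of participants with a 6-month NPI-Q. Enrolment then continues until that number is reached, which at 6.7% loss means about 102 enrolled (104 if the t-based 48 per arm is used).

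In either case, state that the repeat power calculation at the interim will divide the required analysed number by one minus the observed loss rate. Recruitment is already paused for that analysis, so this can be settled now.

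The first option costs one sentence and a slightly less favourable stated power. The second costs about 8 to 10 further participants. Neither changes treatment, assessments or the analysis method.

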### Recruitment and enrollment

Participant recruitment began in 2022 and is paused for a planned interim analysis. Patients are identified through standard clinical workflows in neurology clinics. Eligibility screening and enrollment are performed during routine care encounters, and informed consent is obtained in person or remotely. No financial incentives are offered for participation. Both English- and Spanish-speaking patients are included. All study materials are available in both languages. Spanish-speaking participants are typically consented by bilingual clinicians or research staff, and certified interpreters are used when bilingual staff are unavailable, which is uncommon.

Eligible participants are adults with PD (including PDD) or DLB-related psychosis receiving care at the UTHSCSA or University Hospital Neurology Clinics (the latter is staffed by UTHSCSA Neurology faculty), for whom antipsychotic treatment is indicated. Diagnoses are made by movement disorders specialists during the course of routine clinical management. Clinical equipoise between quetiapine and pimavanserin must exist such that either medication is a reasonable treatment option, and the prescribing clinician must be comfortable prescribing and managing both. Patients meeting criteria are invited to participate by their clinician, who proceeds with enrollment or, if preferred by the clinician, involves a research coordinator to assist.

Exclusion criteria include any medical contraindication to either study medication, absence of a caregiver available to complete the Neuropsychiatric Inventory Questionnaire (NPI-Q)^44^, current use of an antipsychotic at the time of enrollment, or a prescribing clinician who is unwilling to manage both treatment options.

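### The interim at 60 of 94 appears to test the primary endpoint and re-power on effect size, but the only error rate stated is a single two-sided 0.05; used at both looks it would give about 8%, or 9–10% if N is re-set

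*Protocol article*

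**What the plan says.** All the design figures are in Methods, Statistical analysis.

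- **Effect size:** "A prior retrospective comparison of quetiapine and pimavanserin estimated an effect size of 0.58 for psychosis outcomes".
- **Error rate and power:** "a two-tailed α of 0.05, and 80% power".
- **Sample size:** "a total sample size of 94 participants (47 per arm) was calculated using a standard two-sample comparison of means".
- **Interim:** because the effect estimate came from retrospective data and may be off, "an interim analysis has been planned for once 60 participants enrolled", "including a repeat power calculation if the primary endpoint has not yet been reached".

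The same section says that outcomes are analysed by intention to treat and that missing data are left out.

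Recruitment and enrollment reports: "Participant recruitment began in 2022 and is paused for a planned interim analysis". The enrolment summary in the main text before Methods counts 56 of 60 as retained, "including 48 who have completed the study and 8 who remain active with a mean time since enrollment of 130 days", and four as lost. Randomization and interventions states that the allocation is open to everyone once assigned.

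The article gives no interim significance level, boundary, spending rule or stopping rule. It does not say whether the repeat power calculation is blinded to arm.

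**The concern.** The condition attached to the repeat power calculation makes sense only if the primary outcome is compared between arms at 60 and the result affects what happens next. The reason given for the look is doubt about the treatment effect, not about a nuisance quantity such as the SD, so the re-powering also appears to use the between-arm difference. Both steps can raise the false-positive rate, the first by testing twice and the second by letting the final N depend on the observed effect.

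Beside these steps stand one alpha of 0.05 and an N that is correct for a single analysis at that level. Read as written, the stated alpha describes a one-look trial and the procedure describes something else. Recruitment is already paused for the interim and treatment is open-label, so a boundary chosen after the comparison has been seen could no longer protect the error rate.

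**Working it through.** **Inputs.** Effect size d = 0.58, two-sided alpha 0.05, power 80%, 47 per arm and the interim at 60 enrolled come from Statistical analysis. The 1:1 ratio comes from Randomization and interventions. The 48 completed, 8 active and 4 lost come from the enrolment summary. The caps on a re-set N are assumptions, since the article gives none.

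**1. The plan's own N.** n per arm = 2 × [(1.960 + 0.842)/0.58]² = 46.7, rounded up to 47, total 94. Power at 47 per arm is 80.3% by the normal approximation. The t-based version gives 47.6, or 48 per arm. So 94 is reproduced at the full 0.05 with no sequential inflation.

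**2. Two looks at 0.05, N kept at 94.** Under no treatment difference the two test statistics are bivariate normal with correlation √t, where t = outcomes at the look ÷ 94. The overall error is 1 − P(|Z₁| < 1.96 and |Z₂| < 1.96).

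| Outcomes at the look | t | √t | Overall two-sided error |
|---|---|---|---|
| 60 | 0.638 | 0.799 | 7.8% |
| 56 | 0.596 | 0.772 | 8.0% |
| 52 | 0.553 | 0.744 | 8.1% |
| 48 | 0.511 | 0.715 | 8.3% |

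Simulated t-tests at 30 and 47 per arm give 7.7%. If the final analysis also loses participants (56 of 90), the result is 7.9%.

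**3. N re-set from the observed effect.** Simulation under no difference, with 30 per arm at the look. If the interim is not significant at 0.05, the new n per arm is 2 × (2.802/d̂)², where d̂ is the observed standardised difference, bounded below by 31 or 47 and above by the cap. The final test is at 0.05 on all data.

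| Assumed cap per arm | 0.05 at both looks | No efficacy test at the interim, re-sizing only |
|---|---|---|
| 100 | 9.1% | 6.2–6.6% |
| 150 | 9.5% | 6.6–7.0% |
| 300 | 10.0% | 7.1–7.5% |

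The ranges in the last column are for lower bounds of 47 and 31 per arm. With no efficacy test and N kept at 94, or with re-powering on a blinded pooled SD, the error stays at about 5%.

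**4. What would hold 5% with N at 94.** For Lan-DeMets O'Brien-Fleming-type spending at 0.025 per tail, the interim two-sided level is 4 × [1 − Φ(2.241/√t)]. The final level is then solved so that the total is 5%.

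| Outcomes at the look | Interim p | Final p | Power at 94, d = 0.58 |
|---|---|---|---|
| 60 | 0.010 | 0.047 | 79.9% |
| 56 | 0.007 | 0.048 | 80.0% |
| 48 | 0.003 | 0.049 | 80.1% |

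Fixed-sample power is 80.3%, so the loss is at most 0.4 of a percentage point. The levels move with the number of outcomes, so the spending function should be fixed and not a pair of p-values.

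**5. A boundary alone is not enough if N moves.** Applying the 0.010/0.047 boundary and then re-setting N as in step 3 gives about 6–7% across the same caps. Re-sizing needs its own protection.

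**The case against.** The strongest reply is that this is a condensed article. An approved protocol exists and is not shown, and interim boundaries are commonly left to it or to the SAP. Three stronger readings are tempting, and the text supports none of them.

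- **That alpha is in fact unadjusted.** The 0.05 is an input to the sample-size calculation. Nowhere does the article say that each look is tested at 0.05. Nor does N = 94 settle it: a final level of 0.047 needs 2 × [(1.986 + 0.842)/0.58]² = 47.5, or 48 per arm, which is hardly different from 47. An O'Brien-Fleming-type rule elsewhere cannot be excluded.
- **That the trial stops at p < 0.05.** Only the repeat power calculation is made conditional; no efficacy stop is stated. A reader might go on to infer an exaggerated effect at early stopping (with a true effect of 0.58, stopping about 61% of the time with a mean estimate near 0.74). That rests wholly on an assumed stop at 0.05.
- **That the look will run before the 8 active participants finish.** The 48 and 8 describe status when the article was written, not an interim data cut. A recruitment pause is equally consistent with waiting for follow-up.

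These replies make the size of the problem conditional. They do not remove the mismatch on the page: a result-dependent interim and effect-driven re-powering sit beside one fixed-sample alpha, and the trigger is stated as enrolment.

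**Conclusion.** The point holds in conditional form. The article implies a between-arm look at the primary endpoint at 60 of 94 and a repeat power calculation driven by the effect size, and it states only a single two-sided 0.05 with a fixed-sample N.

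If 0.05 is used at both looks, the type I error would be about 8% with N at 94 (7.8% with 60 outcomes, 8.3% with 48). It would be about 9–10% if N is re-set from the observed effect, under assumed caps of 100 to 300 per arm. It would be about 5% if the interim does not test efficacy and either N stays at 94 or re-powering is blinded. Which case applies cannot be told from the article. It should be settled in writing before the data are opened.

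**What to change.** Before the interim data are opened, add one paragraph that does the following.

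1. **Interim test.** Specify a Lan-DeMets O'Brien-Fleming-type spending function, evaluated at the number of outcomes actually available (at 60 of 94, nominal two-sided p of about 0.010 at the interim and 0.047 at the end). Alternatively, state that the interim does not test for efficacy.
2. **Repeat power calculation.** Base it on the pooled SD, blinded to arm. If N may change on the observed effect, name a combination or conditional-error test for the final analysis.
3. **Timing.** Run the look once the 60 enrolled have finished follow-up, not at the 60th enrolment. Some of the 60 may still lack an outcome, and the spending function allows for that.

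The cost is that paragraph and less than 1 percentage point of power at 94. A combination or conditional-error test adds some complexity to the final analysis; the blinded option avoids it. If the full protocol or SAP already sets such a boundary, it is enough for the stated alpha to refer to it and for the re-powering basis to be made explicit.

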## Data Availability

The datasets generated and/or analyzed during the current study are not publicly available because the trial is ongoing and to protect patient privacy, but are available from the corresponding author on reasonable request after trial completion, through a data sharing agreement.
